**INTRODUCTION**

**Background**

Obesity is an epidemic, recurrent and progressive pathological process with many causal factors (Bray et al.,2017). Obesity affects about 650 million people, or 13% of the world’s adult population (Haththotuwa et al.,2020). In this scenario, obesity represents a fundamental public health clinical problem, as it increases the risk of cardiovascular disease, insulin resistance, cancer, osteoarthritis (Haththotuwa et al.,2020) as well as complications of postural control and alterations in physical performance (Cahill et al.,2013; Gupta et al.,2017 ). For obese people, lifestyle changes such as changing eating behaviors and increasing physical activity are generally recommended and known to be major components of weight reduction programs (Bellicha et al.,2021). In recent years, time restricted eating (TRE) has emerged as an intermittent fasting diet and a potential alternative to continuous calorie restriction CCR (O'Connor et al., 2021), which has been shown to improve cardiometabolic health, insulin sensitivity, blood glucose levels, lipid profile, blood pressure (Rynders et al.,2019), as well as improved liver function, intestinal microbial diversity and circadian gene expression (Zeb et al.,2020), and decreases oxidative stress (Sutton et al.,2018). TRE becomes a popular strategy because it is easy to follow for a longer period of time and does not require people to limit their overall food intake or calculate total daily calorie intake, which can improve adherence (O'Connor et al.,2021).

Moreover, regular physical activity remains one of the most powerful treatments to combat obesity (Bellicha et al.,2021). The American College of Sports Medicine recommends at least 150 min/week of moderate intensity aerobic activity or 75 min/week of vigorous intensity to improve health, and 225 min/week or more is recommended for weight loss/maintenance (CMHA , 2013). However, compliance with these guidelines is low, and is a frequently cited obstacle (e.g., walking/running fast), which is perceived as repetitive and boring and takes time (ACSM, 2013; Ekkekakis et al.,2022). In order to reduce the time spent on exercise, high intensity interval training (HIIT) has recently gained popularity as a good exercise choice for obese people (Andreato et al.,2019). This type of exercise consists of short periods of high intensity activity followed by periods of rest or low intensity (Gillen et al., 2014; Andreato et al., 2019). Cycling, running and rowing are traditional exercise modalities that have adapted HIIT protocols, but for people who exercise for health and leisure, these traditional modalities seem boring and do not engage people because of the monotonous nature of the exercise associated with repetition (Sharp et al.,2022). An alternative to HIIT is high intensity functional training (HIFT), a relatively new training modality that includes a combination of aerobic exercise and resistance and consists of alternating short periods of intense exercise with periods of rest or active recovery of moderate intensity using movements multi-functional varied articular.

HIFT is generally performed in a circuit training format at high relative intensities, with the aim of simultaneously improving all physical attributes (Feito et al.,2018). In overweight/obese adults with type 2 diabetes mellitus, Nieuwoudt et al. (2017) showed significant improvement in beta cell function, while decreasing body fat and preserving lean mass after 6 weeks of HIFT. Similarly, Fealy et al.,2018) reported improvements in cardiometabolic risk factors with HIFT training. Research indicates that HIFT is superior to HIIT to improve health (Heinrich et al.,2014; Fisher et al., 2017). With respect to the combination of exercise and fasting, there are few studies that have investigated the combined effect of TRE and endurance/resistance training on body composition and performance parameters in healthy individuals (Moro et al.,2020; Tovar et al.,2021), but little is known about the metabolic benefits of this combined therapy in a sedentary overweight/obesity population.

**TRIAL OBJECTIVES**

**Primary Objective**

The primary objective of the study is to investigate the isolated and combined effects of 12 weeks of TRE and HIFT on weight and body composition in inactive obese women.

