**Primary Outcome**

Primary Outcome include the effect of the separate and combined effects of 12 weeks of early TRE (i.e., consuming all calorie intake between 8:00 a.m. and 4:00 p.m. daily) and HIFT (three exercise sessions per week), on body composition in women with obesity.

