**Randomization**

Participants will be randomized in a 1:1:1 manner to TRE, HIFT and TRE-HIFT groups using a web-based system for random number generation by a person independent of the research group. Participants in the combined group (TRE-HIFT) followed the same exercise protocol as per the HIFT group and the same TRE protocol as the TRE group.

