**TRE intervention**

Participants will be asked to consume all their food during an 8-hour period (from 8:00 am to 4:00 pm) each day for the next three months. Over the remaining 16 hours each day, participants can drink, but only non-calorie drinks (e.g. water or coffee/tea with no milk or sugar).

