**HIFT intervention**

HIFT will be performed 3 days per week in the evening at the fasting window (i.e. 5:00 p.m.). All HIFT sessions include 5 minutes of dynamic warm-up and 5 minutes of cool-down, in addition to 45-55 minutes of HIFT. Each HIFT session corresponds to 8 series of 8 functional exercises (aerobic and resistance) based on Tabata training. All exercises will be performed with body weight or with free weights (e.g. dumbbells, kettlebell, weight plate) using a self-selected pace and weight/resistance. Participants should perform as many repetitions as possible of a given exercise for 20 or 30 seconds, followed by a 10-second rest. There were 2 minutes of rest between each exercise.

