***Final follow-up at 12 weeks:***

- Weight
- Blood pressure
- Blood Lipid profile and glucose level
- IPAQ
- TRE adherence

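### The primary objective and outcome claim isolated and combined effects of TRE and HIFT, which the three randomised arms, with no neither-treatment arm, can support only in part

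*Protocol*

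**What the plan says.** The Protocol's Primary Objective is "to investigate the isolated and combined effects of 12 weeks of TRE and HIFT on weight and body composition" in inactive obese women. The Primary Outcome section uses parallel wording, "the effect of the separate and combined effects of 12 weeks of early TRE", and goes on to HIFT and body composition.

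The arms are fixed in the Randomization section: "Participants will be randomized in a 1:1:1 manner to TRE, HIFT and TRE-HIFT groups". The same section defines the combined arm by reference to the other two: "Participants in the combined group (TRE-HIFT) followed the same exercise protocol as per the HIFT group and the same TRE protocol as the TRE group".

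The intervention sections describe only the two active components: TRE ("Participants will be asked to consume all their food during an 8-hour period") and HIFT ("HIFT will be performed 3 days per week in the evening at the fasting window"). No section describes an untreated, usual-care or waiting-list group. Outcomes are measured at baseline and once more at 12 weeks.

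The protocol states no sample size, standard deviation, significance level or statistical test. It makes no statement about synergy, additivity or interaction.

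**The concern.** Because the combined arm is exactly the two single-component protocols given together, the arms are three cells of a 2x2 layout. The missing cell is the one with neither component. In ordinary usage, the isolated effect of an intervention is what it does compared with not having it, and that comparison needs the missing cell. So does the effect of the combination against no intervention.

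What is at stake is what the trial may conclude on its primary question. If the objective stays as worded, the only ways to report an isolated effect are a before-after change within one arm or an unstated assumption that the two components do not interact. The first is not a randomised comparison: it mixes the intervention with passage of time, season, the effect of taking part and regression to the mean. The second cannot be checked with these arms. An analysis plan cannot repair this, because the missing arm is a feature of the allocation.

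**Working it through.** **Inputs.** The arms and the content of the combined arm come from the Randomization section. The quantities claimed come from Primary Objective and Primary Outcome. There is no stated figure to reproduce, so the check is one of estimability.

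**Model.** Write the mean 12-week change as

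E[change] = b0 + bT·TRE + bH·HIFT + bTH·TRE·HIFT,

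where b0 is the change expected with neither component. The arm means are then:

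- TRE: T = b0 + bT
- HIFT: H = b0 + bH
- TRE-HIFT: TH = b0 + bT + bH + bTH

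The design matrix has rows (1,1,0,0), (1,0,1,0) and (1,1,1,1). Its rank is 3, for 4 parameters. A quantity is estimable only if it is a linear combination of these rows.

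| Quantity | In parameters | Estimable from the three arms? |
|---|---|---|
| TRE alone vs neither | bT | No |
| HIFT alone vs neither | bH | No |
| TRE-HIFT vs neither | bT + bH + bTH | No |
| Interaction | bTH | No |
| TRE added to HIFT: TH − H | bT + bTH | Yes |
| HIFT added to TRE: TH − T | bH + bTH | Yes |
| TRE vs HIFT: T − H | bT − bH | Yes |

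With a fourth concurrently randomised arm receiving neither component, row (1,0,0,0), the rank becomes 4 of 4 and every line is estimable.

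**Under a no-interaction assumption.** Setting bTH = 0 leaves three parameters and rank 3 of 3. Then TH − H = bT, TH − T = bH, and T + H − TH = b0. The isolated effects are recovered, but the three means are used up on three parameters, so nothing is left with which to test bTH = 0.

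**Illustration 1: reading within-arm change as an isolated effect.** The protocol does not plan this test; the sample size and drift below are assumptions. Suppose an intervention is inert but weight or body composition changes for other reasons by δ standard deviations of the change score. A two-sided 5% paired t-test then rejects with probability P(|t′| > t(0.975, n−1)), where t′ is non-central t with non-centrality δ√n.

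| δ (SD of change) | n = 15 | n = 20 | n = 30 |
|---|---|---|---|
| 0.1 | 6.5% | 7.1% | 8.3% |
| 0.2 | 11.2% | 13.6% | 18.5% |
| 0.4 | 30.3% | 39.7% | 56.3% |
| 0.6 | 58.0% | 72.1% | 88.8% |

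The rate depends almost wholly on δ, about which the protocol gives no information. A larger arm makes it worse.

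**Illustration 2: reading the arms as showing how the components combine.** Take invented mean changes T = −3, H = −3, TH = −5 kg, and let C be the unobserved mean change with neither. The interaction is TH − T − H + C = −5 + 3 + 3 + C = 1 + C. The same three results are less than additive if C = 0, additive if C = −1 and more than additive if C = −2 kg.

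**The case against.** The strongest reply is that the objective can be read loosely: isolated and combined may simply mean each intervention given alone and the two given together, which is what the arms are. Active comparators are a legitimate choice, and whether the combination does better than each component alone is a fully randomised question here. Under additivity the single-component effects are estimable as well. All of this stands. It limits the point to the wording of the claim and does not fault the choice of arms. It does not rescue the wording, because both sections speak of effects, and the no-interaction assumption is neither stated nor testable.

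A reader might go further in three ways that the document does not support:

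- **That the trial yields no randomised answer to its primary question.** It yields three valid between-arm contrasts.
- **That the trial will have an inflated false-positive rate.** The protocol specifies no within-arm test, or any test, and the analysis plan is not shown. The percentages above rest on an assumed n and an assumed drift; at 0.1 SD and n = 20 the rate is only about 7%. The entry criteria also require constant weight for three months and exclude recent loss of more than 5%. That limits existing weight trends, though not season or the effect of taking part. A false claim of benefit would also need drift in the favourable direction.
- **That the protocol claims synergy.** It does not, so the second illustration only shows what the arms cannot tell.

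The feasibility aim, to inform later trials, is listed among the secondary objectives and does not change what the primary objective says.

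**Conclusion.** The point holds as a mismatch between the primary claim and the randomised contrasts. As worded, Primary Objective and Primary Outcome cover the effect of TRE alone, of HIFT alone and of the two together. Against no intervention, none of these can be estimated from randomised comparisons, unless an untestable no-interaction assumption is made. This follows from the allocation alone, taking an isolated effect in its plain sense of the component against neither component. It needs no assumption about sample size, variance or effect size. The numerical illustrations carry no weight in the conclusion.

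It should be corrected, because it concerns the primary question, decides what the trial may conclude, and cannot be put right at the analysis stage.

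**What to change.** Reword Primary Objective and Primary Outcome around what the arms support:

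1. Primary: TRE-HIFT minus HIFT, the effect of adding TRE to HIFT.
2. Primary: TRE-HIFT minus TRE, the effect of adding HIFT to TRE.
3. Secondary: TRE minus HIFT.

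Replace the isolated/separate and combined wording in both sections accordingly. Add one sentence saying that within-arm changes from baseline are descriptive and will not be reported as isolated effects of an intervention.

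The cost is a narrower claim than the present one. No participants, arms or measurements change. Keeping the present claim without the no-interaction assumption would need a concurrently randomised arm with neither component; that is not asked for here.

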**Secondary Objectives**

The secondary objectives were to examine the effects of TRE and HIFT on changes in food intake, blood pressure, lipid profile, blood glucose, cortisol and inflammatory biomarkers, and to determine the feasibility of the combined approach (TRE + HIFT) by examining adherence to TRE and HIFT to inform any future randomized trials of the intervention.

**Primary Outcome**

Primary Outcome include the effect of the separate and combined effects of 12 weeks of early TRE (i.e., consuming all calorie intake between 8:00 a.m. and 4:00 p.m. daily) and HIFT (three exercise sessions per week), on body composition in women with obesity.

**Secondary Outcomes**

- Changes in blood pressure from baseline to 3 months
- Changes in lipid profile from baseline to 3 months
- Changes in glucose profile from baseline to 3 months
- Changes in calorie intake from baseline to 3 months
- Adherence to TRE and HIFT

**METHODOLOGY**

**Inclusion Criteria**

- Females aged 18–45 years old
- BMI higher than 30 kg/m^2^
- Waist circumferences higher than 80 cm
- Able to engage in physical activity
- Had not followed a structured training program in the previous 6 months
- Had maintained a constant weight for three months prior to the study

**Exclusion Criteria**

- Having a diagnosis of diabetes
- Having cardiovascular disease
- Smokers
- Using regular medications
- Pregnancy or breastfeeding
- Has lost more than 5% of body weight in the last 6 months
- Currently using TRE or another fasting approach to weight loss.
- Habitual eating window <12 hours/day

**STUDY DESIGN**

**Participant recruitment**

Participants will be recruited recruited using social media advertisements, leaflets and posters in community venues, and word of mouth.

Prospective participants will contact the study team by telephone or e-mail. They will be screened and if eligible, will receive an appointment for the baseline visit and participant information sheet will be sent by post or e-mail.

**Baseline Visit**

At the baseline visit, after completing the consent procedures, eligible participants will complete study questionnaires, and measurements of weight, blood pressure and fasting blood sample collection. Participants will than receive an explanation of the TRE and HIFT interventions and of the follow-up procedures.

**Randomization**

Participants will be randomized in a 1:1:1 manner to TRE, HIFT and TRE-HIFT groups using a web-based system for random number generation by a person independent of the research group. Participants in the combined group (TRE-HIFT) followed the same exercise protocol as per the HIFT group and the same TRE protocol as the TRE group.

**TRE intervention**

Participants will be asked to consume all their food during an 8-hour period (from 8:00 am to 4:00 pm) each day for the next three months. Over the remaining 16 hours each day, participants can drink, but only non-calorie drinks (e.g. water or coffee/tea with no milk or sugar).

**HIFT intervention**

HIFT will be performed 3 days per week in the evening at the fasting window (i.e. 5:00 p.m.). All HIFT sessions include 5 minutes of dynamic warm-up and 5 minutes of cool-down, in addition to 45-55 minutes of HIFT. Each HIFT session corresponds to 8 series of 8 functional exercises (aerobic and resistance) based on Tabata training. All exercises will be performed with body weight or with free weights (e.g. dumbbells, kettlebell, weight plate) using a self-selected pace and weight/resistance. Participants should perform as many repetitions as possible of a given exercise for 20 or 30 seconds, followed by a 10-second rest. There were 2 minutes of rest between each exercise.

**Measures**

***Baseline:***

- Demographic information collected via routine clinic questionnaires
- Weight, BMI
- Blood pressure
- Blood lipid profile and glucose level
- Physical activity levels (IPAQ)

***Final follow-up at 12 weeks:***

- Weight
- Blood pressure
- Blood Lipid profile and glucose level
- IPAQ
- TRE adherence

**Sample Collection, Labelling and Logging**

Blood samples analysis will be conducted by the Doctors laboratory at the University Hospital of Monastir (5000 Monastir, Tunisia).

Samples would be collected by trained phlebotomists in accordance with the Doctors Laboratory instructions, and labelled with participant ID number, time-point/session number, and date.

All samples taken will be logged.

**ETHICS**

The study was carried out in accordance with the Helsinki Declaration and was approved by the “South Human Protection Ethics Committee” (C.P.P.SUD), Sfax, Tunisia: protocol reference C.P.P.SUD N ° 0200/2019, prior to the beginning of the assessments.

